#### Sample size {14}

In this project, the trial group and the control group are to be set up. This study is designed with the control group as the optimal design, and the results are summarized according to previous clinical trials and literature [2]. According to the results of previous clinical trials and literature summary, the first observation index after 12 weeks of treatment was NRS score of neck pain, 1.50 ± 1.70 in the trial group, 2.08 ± 1.65 in the control group; *α* = 0.05 (bilateral test), *β* = 0.10, boundary value 0.08, sample size ratio *k* = 1 in both groups. The PASS software is used to calculate the sample size of 102 cases in the two groups. Considering that the sample size loss rate is about 10–20%, further calculated the sample size of each group is *N* = 120.

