#### Subject recruitment {15}

According to the sample size requirements of 120 cases in the trial group and the control group, this project uses written and online media promotion, broadcast, and other ways to recruit subjects with neck pain to visit Orthopedic Department Outpatients of Shuguang Hospital, Jingzhong Hospital, and Xiangshan Hospital according to the principles of convenient transportation and proximity. The subjects need to go through two baseline diagnostic screenings by clinicians in each research center. The clinicians in charge of diagnosis and screening are not aware of the random grouping. During the scheduled clinical visit, the study clinicians will provide a brief overview of the study. If the participant is interested, the clinicians will determine patient eligibility according to the above eligibility criteria. If the patient is eligible and agrees to participate, the clinicians will conduct the informed consent and enrollment. Participants will be able to discuss study details with the clinicians and ask questions before signing the informed consent. Following enrollment, participants will be randomized by the assistants, who are full-time research assistant in charge of patient grouping, accept their cervical spine examination and imaging examination, and receive the assigned treatment.

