#### Assignment of interventions: randomization

##### Sequence generation {16a}

In this project, a multicenter positive-controlled, randomized clinical trial design is adopted, and subjects who meet the test and research criteria are randomly divided into two groups (proportion of 1:1), which are the trial group and the control group. The random number table was generated by special statistical staff at Shanghai University of T.C.M. According to strict random procedures by using the SAS software (version 9.4, SAS Company, Cary, NC, USA). The randomized list is stored on a secure database (Microsoft Office Access 2007) by the data manager and is inaccessible by the relevant case observer or other researchers. Each subject can only register and randomize once, and no detailed information about the subject can be deleted from the database.

The design procedures of the specific randomized scheme of multicenter clinical trials include randomized parameter setting, randomized regulations, SAS-randomized program design, and the resulting random numbers, randomized coding of the trial center, randomized coding of the trial cases, and randomized coding of the treatment group.
Randomization parameter setting

Seed number, the initial value of the random number, in this study is 151427.

The total number of cases is the sample size. Area group length × area group number = total number of cases: sample size 240 cases, area group length 4, and area group number 60.

Stratification number, taking the center (hospital) participating in the clinical trial as the stratification factor, because the number of cases completed by each participating clinical trial center cannot be determined in advance, the management method of “random center” is adopted in this study; that is, when subjects are enrolled, the person in charge of each participating research center immediately requests the random number and corresponding group code from the “random center” by telephone.

The number of test groups is divided into trial group and control group.

Distribution proportion, the number of samples in each treatment group, is allocated by 1:1.
(2)Randomization rules

Randomization rules for center code distribution

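### N = 120 per group keeps 102 patients with observed data only up to 15% loss, not across the stated 10–20% (minor, but wrong as written)

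*Protocol article*

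**What the plan says.** Section {14} plans on the 12-week pain score, with "1.50 ± 1.70 in the trial group, 2.08 ± 1.65 in the control group". The error rates are α = "0.05 (bilateral test") and β = "0.10, boundary value 0.08, sample size ratio" 1. The result is given as: "The PASS software is used to calculate the sample size of 102 cases in the two groups". The loss allowance follows: "Considering that the sample size loss rate is about 10–20%, further calculated the sample size of each group is" 120. No single rate within that range is named as the one used.

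The figure of 120 is the operative one. Section {15} recruits to it ("According to the sample size requirements of 120 cases in the trial group and the control group"), and the randomisation parameters in {16a} use the matching total: "sample size 240 cases, area group length 4, and area group number 60", with 1:1 allocation.

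Section {20a} bears on what loss means here. Missing values of the main variable in the full analysis set are filled by last observation carried forward, so that the number analysed at the end equals the number at the start. The main variables are to be analysed in both the full analysis set and the per-protocol set.

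**The concern.** The article prints a base size, a loss range and an inflated size, and presents the third as following from the first two. Over the upper half of the range it does not. Anyone who reads {14} as written would take it that a loss of, say, 18% still leaves the calculated number of patients, when it leaves fewer. The allowance for loss is a planning figure that later readers will use to judge whether attrition mattered, so it should say what it actually covers.

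**Working it through.** **Inputs.** From {14}: 102 cases before loss, loss about 10–20%, 120 per group after loss; means 1.50 and 2.08, SDs 1.70 and 1.65; two-sided α = 0.05, β = 0.10, boundary value 0.08. From {16a}: 240 in total, 1:1. Derived: difference 2.08 − 1.50 = 0.58; pooled SD = √((1.70² + 1.65²)/2) = 1.675; distance including the boundary value 0.58 + 0.08 = 0.66.

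**Per group or total?** If 102 were a total, there would be 51 per group, and 51/0.80 = 63.75, so 64 per group would suffice at 20% loss; 120 per group would be unexplained. With 102 per group, 102/0.85 = 120 exactly. The per-group reading is therefore used below, as an inference.

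**Reproducing 120.** Required size = n/(1 − d):

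| Loss d | 102/(1 − d) | Rounded up | Left from 120 |
|---|---|---|---|
| 10% | 113.3 | 114 | 108 |
| 15% | 120.0 | 120 | 102 |
| 20% | 127.5 | 128 | 96 |

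The break-even loss is 1 − 102/120 = 15%. At 20% the shortfall is 102 − 96 = 6 per group, 12 in total, or 6/102 = 5.9%. The cruder rule n × (1 + d) does not rescue the figure: 102 × 1.2 = 122.4, or 123, which is also above 120.

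**What the shortfall costs.** Two-sided t test, α = 0.05, SD 1.675:

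| Distance | Power at 102 | Power at 96 |
|---|---|---|
| 0.66 | 80.0% | 77.5% |
| 0.58 | 69.2% | 66.5% |

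**The base of 102.** With n = 2(z₀.₉₇₅ + z_power)² SD²/Δ²:

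- Δ = 0.66, power 0.80: 2 × 7.849 × 2.806/0.4356 = 101.1, so 102.
- Δ = 0.66, power 0.90: 2 × 10.507 × 2.806/0.4356 = 135.4, so 136 (137 by the t distribution).
- Δ = 0.58, power 0.90: 2 × 10.507 × 2.806/0.3364 = 175.3, so 176 (177 by the t distribution).

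Among the two-sided calculations tried, 102 appears only with the boundary value added and power 0.80. A one-sided 0.05 superiority test at power 0.80 comes close, at 104, but contradicts the stated two-sided test. At the stated β = 0.10 neither distance gives 102.

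**The case against.** The strongest reply is that {14} gives an approximate range and never promises 102 at 20%. Setting N at the midpoint of an expected range is an ordinary choice, and inflating for the worst case is a stricter convention. This stands in part: the defect is that the text attaches 120 to the whole range without naming the rate that produces it, not that 15% was a poor choice.

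Second, under {20a} the full analysis set stays nominally at 120 whatever the attrition. That also stands, and it limits the point to patients with observed data and to the per-protocol set. It does not remove it: the per-protocol set is also named for the main variables, and {14} itself inflates for loss, so the plan does not count lost patients towards 102.

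Third, about 2.5 points of power is small, and uncertainty in the assumed means and SDs could easily exceed it. Agreed.

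A reader might go further and infer that the trial as a whole will end below its calculated size. The documents do not support that. It would need a loss above 15%, it would not apply to the full analysis set count, and it rests on the per-group reading of 102. Nor do the duties described for the data and safety monitoring board in {21a} or {21b} tie a retention threshold to 102, so no misdirected monitoring decision can be read into the plan.

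**Conclusion.** The point holds as a minor error in a stated planning figure. On the per-group reading, 120 covers loss up to 15%; from there to the upper rate of 20% the observed and per-protocol numbers fall below 102, reaching 96 per group (192 instead of 204 in total). The power cost is about 2.5 points on either distance.

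Two qualifications belong with it. The full analysis set count is unaffected, although carried-forward values are not observed 12-week values. And 102 should not be treated as the right target: it matches about 80% power for the 0.66 distance, not the 90% that the stated β implies. A reader might infer that raising N to 128 would put the plan right. It would not, because the stated inputs need 136 or 176 per group before any loss. The base calculation is the larger fault in the same section.

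**What to change.** In {14}, state that 102 is per group, and replace the bare range with what the number covers: N = 120 per group allows for up to 15% loss (102 with observed data), and at 20% loss 96 per group remain. Give the power at 96 for the comparison actually intended: about 78% (77.5%) for a distance of 0.66, or about 67% (66.5%) for a difference of 0.58, by two-sided t test. Note that these counts refer to observed or per-protocol patients, not to the full analysis set after carrying values forward.

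Make the change in the same revision that corrects the base calculation, so that 102 is not restated as delivering β = 0.10. The cost is a sentence or two and a less favourable stated power. This point calls for no extra patients and no retention alert level. The article gives about 31 December 2020 for the end of recruitment, before its publication on 8 February 2021, so a wording change is the practical remedy.

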#### Subject recruitment {15}

According to the sample size requirements of 120 cases in the trial group and the control group, this project uses written and online media promotion, broadcast, and other ways to recruit subjects with neck pain to visit Orthopedic Department Outpatients of Shuguang Hospital, Jingzhong Hospital, and Xiangshan Hospital according to the principles of convenient transportation and proximity. The subjects need to go through two baseline diagnostic screenings by clinicians in each research center. The clinicians in charge of diagnosis and screening are not aware of the random grouping. During the scheduled clinical visit, the study clinicians will provide a brief overview of the study. If the participant is interested, the clinicians will determine patient eligibility according to the above eligibility criteria. If the patient is eligible and agrees to participate, the clinicians will conduct the informed consent and enrollment. Participants will be able to discuss study details with the clinicians and ask questions before signing the informed consent. Following enrollment, participants will be randomized by the assistants, who are full-time research assistant in charge of patient grouping, accept their cervical spine examination and imaging examination, and receive the assigned treatment.

#### Assignment of interventions: randomization

##### Sequence generation {16a}

In this project, a multicenter positive-controlled, randomized clinical trial design is adopted, and subjects who meet the test and research criteria are randomly divided into two groups (proportion of 1:1), which are the trial group and the control group. The random number table was generated by special statistical staff at Shanghai University of T.C.M. According to strict random procedures by using the SAS software (version 9.4, SAS Company, Cary, NC, USA). The randomized list is stored on a secure database (Microsoft Office Access 2007) by the data manager and is inaccessible by the relevant case observer or other researchers. Each subject can only register and randomize once, and no detailed information about the subject can be deleted from the database.

The design procedures of the specific randomized scheme of multicenter clinical trials include randomized parameter setting, randomized regulations, SAS-randomized program design, and the resulting random numbers, randomized coding of the trial center, randomized coding of the trial cases, and randomized coding of the treatment group.
Randomization parameter setting

Seed number, the initial value of the random number, in this study is 151427.

The total number of cases is the sample size. Area group length × area group number = total number of cases: sample size 240 cases, area group length 4, and area group number 60.

Stratification number, taking the center (hospital) participating in the clinical trial as the stratification factor, because the number of cases completed by each participating clinical trial center cannot be determined in advance, the management method of “random center” is adopted in this study; that is, when subjects are enrolled, the person in charge of each participating research center immediately requests the random number and corresponding group code from the “random center” by telephone.

The number of test groups is divided into trial group and control group.

Distribution proportion, the number of samples in each treatment group, is allocated by 1:1.
(2)Randomization rules

Randomization rules for center code distribution

The completion of this study will be done in Shuguang Hospital, Jingzhong Hospital, and Xiangshan Hospital. Each center is sorted into Jing’an J, ShuguangS, and Xiangshan X according to the initials of the hospital abbreviation. Corresponding to the order of “random number of center code distribution” (random number under Center) generated by the SAS statistical software package, the random code of each center is obtained.

Randomization of trial case allocation

This study is divided into two groups: group A is defined as having a Rand of 1, 2, 3, 4, 5, and 6, and group B as having a Rand of 7, 8, 9, 10, 11, and 12.

Randomization rules for distribution of treatment group: this study is divided into two groups. If the first random number is greater than the second random number, group A was the trial group and group B was the control group. Otherwise, group B is the trial group and group A is the control group.
(3)SAS random programming

Using the SAS9.4 unified software, according to the abovementioned random parameters, the software program successively input the seed number corresponding to “proc plan seed,” “random number corresponding to the code of,” title “center,” stratified number corresponding to “factors center” 3; “random number corresponding to the test case of,” title, “factors blocks = 60, Rand = 4,” and other instructions, and then the operation is completed.

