##### Allocation and implementation {16c}

Upon participant enrollment, the diagnostic intervention physician is responsible for asking the person in charge of each participating clinical center for the random number and corresponding group information, and then the person in charge of each participating clinical center immediately asks for the random number and corresponding group code from the “random center” by telephone, and then the person in charge of each clinical center informs the patient of the random number, corresponding group code, and intervention measures by telephone or WeChat. The intervention physician shall not disclose the above information to the subject and the symptom and sign information collection physician.

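### A fixed block length of 4 makes up to one third of allocations predictable if blocks run within center, and the sections on block structure and on who knows the codes contradict each other

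*Protocol article*

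**What the plan says.** **Block structure.** Sequence generation {16a} sets "sample size 240 cases, area group length 4, and area group number 60", with 1:1 allocation, "taking the center (hospital) participating in the clinical trial as the stratification factor". The SAS description repeats the length: "factors blocks = 60, Rand = 4". Center is coded in a separate statement. The same section also states that "group A is defined as having a Rand of 1, 2, 3, 4, 5, and 6, and group B as having a Rand of 7," and so on up to 12. The seed is printed: "Seed number, the initial value of the random number, in this study is 151427". No varying lengths are mentioned, and nothing says that the length is withheld from sites.

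**Who requests and who knows.**
- Subject recruitment {15}: "The clinicians in charge of diagnosis and screening are not aware of the random grouping"; full-time research assistants randomize after enrollment.
- Concealment mechanism {16b}: center heads and diagnostic intervention physicians do not know the random numbers or groups.
- Allocation and implementation {16c}: "the diagnostic intervention physician is responsible for asking the person in charge of each participating clinical center for the random number" and the group information. The center head then telephones the random center. The intervention physician is told not to pass the information on, which implies that this physician has it.
- Data collection {18a}: the person in charge of each center is entitled to obtain the grouping data.
- Blind implementation {17a}: only subjects and data analysts are listed as blinded.

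**The concern.** Telephone allocation hides the list itself. It does not stop someone from working out the next code from the codes already issued. With a fixed short block, anyone who knows the length and has kept count at a site knows the last place in every block and sometimes the third. Keeping count needs no breach of procedure, because manipulation and capsules look nothing alike.

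Staff who can foresee the arm can delay, advance or discourage a patient according to expected outcome. That is selection bias. Here the primary outcome is self-rated pain, and the stated aim is to show that manipulation is better. Adjustment for measured baseline variables would remove part of such a bias, but not the part that comes from unmeasured prognosis or expectation.

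**Working it through.** **Inputs.** Block length 4, 60 blocks, 240 patients, 1:1 ratio, 3 centers, and the rule on Rand values 1 to 12, all from Sequence generation {16a}. Assumptions, not in the article: staff know the length and track earlier allocations; the recruitment split between centers; 80 patients per center for the varying-block simulation.

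**The plan's own figure.** 4 × 60 = 240. It reproduces. The article gives no predictability figure.

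**Reading 1: blocks of 4 run within center.**
- Certain in advance: the 4th place always (1), and the 3rd place when the first two match (probability 1/3). Sum 1 + 1/3 = 1.333 per block.
- 1.333 / 4 = 33.3%; 0.333 × 240 = 80 patients.
- Probability of a correct best guess by place: 1/2, 2/3, 2/3, 1. Sum 2.833; 2.833 / 4 = 70.8%, against 50% with no information.

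**Reading 2: blocks of 12, as the Rand rule implies.**
- With a block of 2m, the expected number of certain places is 2m/(m+1). For m = 6: 12/7 = 1.714.
- 1.714 / 12 = 14.3%; 240/7 = about 34 patients. Best guess 64.3% (by enumeration).
- This reading does not fit the other parameters: 12 × 60 = 720, not 240. Conversely, Rand values of 1 to 4 would all fall in group A under the stated rule. The two statements cannot both stand.

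**Reading 3: one list of 60 blocks of 4 shared by three centers.** Each center sees only its own patients but is generously assumed to know its position in the block.
- For a center with recruitment share p, a place is certain only if both earlier patients who fix it were its own. The share certain at that center is (1 + 1/3)/4 × p² = p²/3.
- Averaged over patients: (Σp³)/3.
- Equal centers: 3 × (1/3)³ / 3 = 1/27 = 3.7%.
- Assumed split 60/20/20: (0.216 + 0.008 + 0.008)/3 = 7.7%; simulation gave 7.8%.

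**Effect of varying the length (simulated).** With random lengths within center, 80 patients per center, and staff who know the set of lengths but not their order, the share certain in advance is about 5.5% for lengths 4/6 and 2.2% for 4/6/8, against 33.3% for fixed 4.

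**Concealment sections side by side.** {16b} says center heads and intervention physicians do not know the groups. {16c} sends every code through the center head at the physician's request, and {18a} gives the center head access. {15} assigns randomization to assistants; {16c} gives the request to the physician. These cannot all describe one procedure.

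**The case against.** A reader might infer that sites do know a third of allocations before they enroll a patient. The article does not support that.
- Running blocks within center is one reading. The program makes 60 blocks in one statement, and center totals are said to be unknown in advance, which fits a shared list as well.
- Section {16c} places the request at enrollment. Section {15} has screening clinicians, unaware of grouping, decide eligibility and take consent first. Nothing says that the physician who requests the code is the one who screens; Intervention description {11a} describes separate treating teams whose initial diagnosis follows entry to the group.
- Three clinicians treat at each center (two for manipulation, one for the drug), so each would have to pool and order colleagues' cases. Only the center head plausibly holds the whole sequence.

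Nor does the article show that printing the seed and length exposed the sequence. It appeared on 8 February 2021, after the planned end of recruitment on 31 December 2020 (Trial status). The registry copy and the site procedures cannot be seen.

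These points limit the size of the problem and bar any claim that codes were in fact foreseen. They do not remove it. The length of 4 is stated twice, those who treat know the arm, and the safeguards in {15} and {16b} are undercut by {16c} and {18a}.

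**Conclusion.** The point holds in conditional form. A fixed block of 4 with center as stratum makes up to 33.3% of allocations (80 of 240) predictable, provided that blocks run within center and that someone at the site knows the length and all earlier assignments. Depending on which unresolved statement is followed, the share lies between about 4% and 33%: 3.7–7.7% for a shared list (the upper figure rests on an assumed 60/20/20 split), 14.3% for blocks of 12, 33.3% for blocks of 4 within center. The shared list lowers predictability only by giving up the stated stratification, so that reading needs correction too. The firmest defect is that the sections on block structure and on who knows the codes disagree. Whether any allocation was actually anticipated cannot be told from the article.

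**What to change.** **For patients not yet randomized.**
- The random center issues a separate list for each center, with block lengths varying at random (for example 4, 6 and 8). The lengths and the seed stay at the random center and out of any document that sites use.
- Reconcile {15}, {16b}, {16c} and {18a} so that the research assistant named in {15}, not the diagnosing or treating physician, requests the code after eligibility and consent are locked. State who learns the group and when.
- Correct the Rand rule so that it agrees with the block lengths used.

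**For patients already randomized** (possibly all, given the dates in Trial status).
- State which scheme was used: block length, and per-center or shared list. State who knew the length and the earlier codes.
- Check baseline balance by predictability. For each patient, compute the probability of manipulation implied by earlier allocations in the block (0, 1/3, 1/2, 2/3 or 1 for a block of 4), then examine within each arm whether baseline pain and other prognostic variables vary with it.

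**Cost.** A revised program and list, an amendment of a few sentences, and care in handling two lists if the change comes during recruitment. An unfinished block can leave an imbalance of at most half its length: 8/2 = 4 patients per center instead of 4/2 = 2. The baseline check uses data that the trial already collects.
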